### Recruitment

Patients eligible for the DEFeND trial will be screened through outpatient clinics and weekly Head and Neck Multidisciplinary Team meetings. The steps that will be completed on all patients to ensure they meet enrolment criteria include the following:
Clinical examinationDetailed medical history including previous treatment/surgery to the head and neckClinical decision to offer a lateral neck dissection

Screening will be performed upon a patient’s possible eligibility for the study as above and will be documented in a secure online ‘Screening log”’ managed by the Liverpool Cancer Trials Unit (LCTU). There are no restrictions regarding concomitant care or interventions during the trial.

Eligible patients should be approached within the outpatient setting and provided with a full explanation of the trial. The patient should also receive an up to date version of the Patient Information Sheet (PIS) (see Additional file 2). Once the patient has had the opportunity to read the PIS and ask any questions, they may consent to the trial (see Additional file 3). The removal of a (24 h) cool-off period prior to signing the consent form has been agreed by the REC; the patient is simply given as much time as they deem necessary. The rationale for such an approach was to reduce patient burden; the recruiting hospitals are tertiary centres with many patients travel long distances to attend appointments. Harmonising the research process with standard clinical care appointments seeks to avoid extra hospital visits, allowing patients the option to provide study consent on the day of being approached.

The DEFeND trial requires that completed consent forms are securely uploaded to the LCTU’s online portal with the patient’s identifiable data still visible. The consent forms will be checked by two independent members of the central trial team. Once these checks have taken place and the consent considered valid, the uploaded document will be permanently deleted from the portal. Any further reference to the consent will need to be performed by accessing the original hard copy stored at the site in the patient’s medical records.

### Allocation

Randomisation lists will be computer-generated by the statistician prior to the recruitment of the first patient. Patients will be randomised using a 1:1 ratio. Lists will be produced based on the principle of randomly permuted blocks with random block sizes of 2 and 4. Patients will only be stratified according to the hospital in which they receive their treatment.

The process of randomisation will be undertaken pre-operatively using the “Treatment Allocation RanDomIsation System” (TARDIS) software version 3.8. This software has been developed by the LCTU. The allocation will be concealed to everyone including the person performing the randomisation. Once randomisation has been performed, the surgeon caring for the patient will receive an automated email which contains a link to reveal the allocation. Once the patient has undergone their neck dissection immediately prior to the point of wound closure, the surgeon will open the link and login to TARDIS to reveal the allocation. The exact time and date this occurs will be recorded and cross-referenced against the start and finish times of surgery as a quality assurance step to minimise performance bias. The randomisation process can be performed either centrally or at the site once the eligibility criteria have been entered and signed off by the Principal Investigator.

As part of the blinding strategy, any clinicians who will be assessing study outcomes must leave theatre prior to the revealing of treatment allocation. They must not return until the theatre has been cleared of any evidence of FS usage. The surgeon administering the FS will not be allowed to assess study outcomes for the patient and must delegate this responsibility to a suitable colleague.

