## Methods/design

### Trial design

This is a randomised external pilot trial set within two UK hospitals offering tertiary head and neck surgery services (Aintree University Hospital NHS Foundation Trust & Queen Victoria Hospital NHS Foundation Trust). Both institutions serve a large population with a mix of both urban and rural communities. Aintree University Hospital treats a population that includes the most deprived 10% of the UK [16]. The target population for this study is patients that are due to undergo lateral neck dissection as part of their treatment for Head & Neck Cancer.

The study design that is being piloted is that of a two-arm, parallel group, superiority trial with block randomisation in a 1:1 allocation ratio. The interventional arm will constitute the application of FS (Artiss, Baxter Healthcare Ltd.) to the surgical wound in addition to standard of care (SOC), and the control arm will constitute SOC alone. For the purposes of this study, SOC constitutes the surgeon performing the neck dissection as they normally would and establishing complete haemostasis. Patients in both arms will have a single surgical drain placed and the wound closed with resorbable sutures across the platysma layer and metal clips to close the skin. The use of FS or any other adjunct to haemostasis in neck dissection is not a common place within the UK. For this reason, the selection of SOC as the comparator is justified. The Consolidated Standards of Reporting Trials (CONSORT) diagram is shown in Fig. 1.

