**Fig. 1 Fig1:**
[figure not shown]
Study flow diagram (CONSORT diagram)

The protocol has been prepared in line with the Standard Protocol Items: Recommendations for Interventional Trials (SPIRIT) guidelines. The SPIRIT Figure shows the different data collection steps of the pilot trial (Table 1); a completed SPIRIT checklist is available as an additional file (Additional file 1).

**Table 1 Tab1:** Schedule of assessments (SPIRIT figure)

Procedures	Head and Neck Clinic/MDT	Screening	Pre-operative assessment	Baseline*	Day of surgery (day 0)	Follow-up schedule				Premature discontinuation
						Daily in-patient assessment	Follow-up 1 (days 7–14)	Follow-up unscheduled	Follow-up 2 (days 28–42)	
Identify potential participant	X	X								
Approach potential participant to discuss study	X	X								
Medical history		X								
Physical examination		X								
Assessment of eligibility criteria		X								
Review of concomitant anticoagulant medications		X	X	X	X	X	X	X	X	X
Review of previous treatment to the ipsilateral neck		X								
Demographic assessment		X								
Signed consent form				X						
Randomisation				X						
Assessment of patient-reported outcome measures										
Neck pain (VAS)				X		X	X	X	X	X
Neck Dissection Impairment Index (NDII)				X					X	X
Wound Healing Questionnaire (WHQ)									X	X
Surgical protocol										
Neck dissection surgery					X					
Allocation revealed at point of wound closure					X					
Prepare and administer ARTISS (interventional arm only)					X					
Assessment of clinical outcome measures										
Assessment of AEs (Clavien-Dindo)					X	X	X	X	X	X
Wound drainage volume (ml)						X				
Wound drain removal						X				
Hospital discharge						X				
Assessment of pilot study outcomes										
Assessment of blinding strategy									X	X
Assessment of minimal clinically important Difference									X	X
Laboratory tests										
Full blood count**				X						
INR & APTT				X						
Pregnancy test (women of childbearing age)				X						
Histological lymph node yield									X	

*VAS* visual analogue scale, *INR* international normalized ratio, *APTT* activated partial thromboplastin time

*At baseline, all procedures should be done before study intervention

**Full Blood Count must include haemoglobin concentration, platelet count and white cell count

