The administration of FS requires at least 3 people including a scrub practitioner, assistant and surgeon. While the FS is being thawed, the surgeon should irrigate the wound with 100 ml of sterile normal saline, dry the wound with sterile gauze swabs, secure the surgical drain and place several resorbable parachute sutures (4–6) across the platysma layer. These sutures should be loosely clipped and not tied to ensure good access to the wound. The drain should be held temporarily outside of the wound to ensure the perforations are not occluded by the FS. The prepared Sprayset should not be held any closer than 10 cm to the wound to avoid the risk of air embolism. Once the administration of FS has commenced, the surgeon has 60 s to deliver up to 2 ml and manipulate the skin flaps into position prior to polymerisation. It is therefore important to strictly adhere to the time using a stopwatch. The assistant should retract any structures (e.g. sternocleidomastoid muscle) to ensure the surgeon can reach sheltered areas and administer the FS evenly in a thin layer across the entirety of the wound. Once the administration is complete, the drain and skin flaps are repositioned and even pressure applied to the wound (using a large rolled-up gauze swab) while the surgeon ties off all of the parachute sutures. It is very important that the surgeon does not lift the skin edges up while tying the sutures as this may break any adhesive bond between tissue layers. The surgical vacuum drain should then be activated, and the assistant should maintain pressure on the neck for a full 3 min. After 3 min, clips/staples are used to close the skin edges. When spraying the FS, changes in blood pressure, pulse, oxygen saturation and end-tidal CO_2_ should be monitored because of the possibility of air embolism.

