### Blinding

Patients, clinical outcome assessors, ward staff and research staff both centrally and at the site will be blinded to the allocation. Only members of the surgical team present in the theatre when the allocation is revealed will know which treatment arm the patient has been allocated to. These individuals are not permitted to inform colleagues or assess trial outcomes. The operation note, medical case notes and any other documentation that leaves the operating theatre will not state the allocation. The effectiveness of this blinding strategy will be assessed using blinding indices.

The patient will be unblinded if they suffer a serious adverse event and knowledge of the allocation is required for the ongoing medical management of the condition. It is unlikely that this trial will require unblinding as the FS is administered only once in the theatre environment. A severe hypersensitivity reaction, air embolism or transmission of an infective agent constitute a serious adverse event. If they occur, severe hypersensitivity and air embolism would be anticipated to occur during or immediately after administration in the theatre setting. Staff caring for the patient at this time will not be blinded, so there will not be a delay in diagnosis and emergency management.

In the event that the patient is diagnosed with an infectious disease that was not diagnosed pre-operatively, they will be unblinded. Based on the ‘Serious Hazards of Transfusion’ 2017 annual report [24], the following infectious diseases are known to have been transmitted via blood products in the UK:
Hepatitis A, B, C or EHuman immunodeficiency virus (HIV)Parvovirus (B19)Cytomegalovirus (CMV)Human T cell lymphotropic virus (HTLV) types I and IIMalariaVariant Creutzfeldt-Jakob Disease (vCJD) or any other prion disease

If the patient is newly diagnosed with any of the above infectious diseases, they will be unblinded and immediately referred to the appropriate medical specialists for treatment.

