### Adherence to the protocol

While every effort has been made to harmonise the protocol with standard clinical/research practice, there will inevitably be some challenges with adherence.
i)The use of eCRF is new to both research sites and requires real-time data entry. This will require training and logistical planning by sites to ensure there are sufficient research staff available (including weekend cover).ii)The allocation needs to be revealed at a specific time point during surgery. This requires surgeons to access their email, login to the randomisation software (TARDIS) and reveal the allocation. To minimise performance bias, the allocation must not be revealed too early; this will be monitored by recording the date and time the allocation is revealed and cross-referencing this with the start and finish times of surgery.iii)The blinding strategy may be difficult to enforce within busy clinical practice. The surgeons present in theatre at the time of the allocation reveal are not allowed to assess trial outcomes. In standard clinical practice, it is routine for the operating surgeon to review their patient post-operatively; eliminating their influence on outcomes including the patient’s perception of outcomes will be difficult. If it is known that a particular surgeon will be reviewing the patient post-operatively, they will be asked to vacate theatre at the time of the reveal.iv)Patients are required to attend two planned follow-up appointments after surgery. The first at 7–14 days to coincide with the removal of skin clips and the second at 4–6 weeks to coincide with the first routine clinic appointment. It is possible that this schedule will clash with some follow-up arrangements and necessitate patients making extra visits. A modest financial refund for travelling expenses will be offered to patients for any extra visits.

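### The rule for outcome assessors' return to theatre is tied to clearing sealant evidence, which only one arm can produce, so the time of return can hint at the allocation

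*Protocol article*

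**What the plan says.** The protocol article's Allocation section sets the reveal late in the operation: "immediately prior to the point of wound closure, the surgeon will open the link and login to TARDIS to reveal the allocation". The rule for leaving is the same in both arms: "any clinicians who will be assessing study outcomes must leave theatre prior to the revealing of treatment allocation". The rule for coming back is: "They must not return until the theatre has been cleared of any evidence of FS usage".

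Only one arm can generate such evidence. The schedule of assessments (Table 1) lists the step "Prepare and administer ARTISS (interventional arm only"), and Trial design says that "the control arm will constitute SOC alone". No sham preparation, waiting or clearing is described for SOC.

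The Blinding section states the aim: "Patients, clinical outcome assessors, ward staff and research staff both centrally and at the site will be blinded to the allocation". It also forbids theatre staff from telling colleagues and keeps the allocation out of documents that leave theatre. Adherence to the protocol, in the Discussion, adds that a surgeon expected to see the patient after the operation is to step out when the allocation is revealed. It does not say when that surgeon may come back.

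**The concern.** The exit rule does not depend on the arm, but the return rule does. In an SOC case there is nothing to clear, so the stated condition is already met at the reveal, with the wound not yet closed. In an FS case it is met only after the sealant has been prepared and applied, pressure has been held and the equipment removed. The bans on telling colleagues and on recording the arm do not cover information carried by the time of return.

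Those affected are the people the blind is meant to protect. They grade complications by Clavien-Dindo and may judge fitness for discharge, both of which involve judgement; the article itself notes imperfect inter-observer reliability for that classification. Testing the blinding strategy is also a stated objective and outcome of this pilot. The assessment of blinding, scheduled at follow-up 2 or premature discontinuation, would register an overall loss of blinding but would not identify this rule as a cause. An avoidable leak could then be mistaken for a limit on what blinding can achieve in phase III.

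**Working it through.** The article states no figure on this point, so there is none to reproduce. The check has two parts.

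**1. Is there a return criterion common to both arms?**
- Allocation: leaving is tied to the reveal (both arms); return is tied to clearing FS evidence (FS arm only).
- Blinding: restricts speech and documents, with no return time.
- Adherence to the protocol: covers leaving at the reveal, not return.
- Trial design and Table 1: FS in one arm, no sham step in the other.

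None of these sections gives a common criterion.

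**2. How large a timing difference do the article's own step times imply?**

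Inputs, all from the section on storage, preparation and administration of FS:
- Thaw: 5 min. The surgeon irrigates and dries the wound, secures the drain and places sutures while the sealant thaws, so some or all of this time overlaps with closure preparation.
- Application window: 60 s.
- Pressure: 3 min ("the assistant should maintain pressure on the neck for a full 3 min").
- Clearing of equipment: no time given.

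Extra time in the FS arm before clearing:
- Thaw fully overlapping: 1 + 3 = 4 min.
- Thaw not overlapping at all: 5 + 1 + 3 = 9 min, which is the upper end.

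To translate this into guessing, suppose assessors return as soon as theatre is clear, and that reveal-to-return time is normal with the same SD in both arms and means d minutes apart. An assessor who knows both distributions and cuts at the midpoint is right with probability

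p = Φ(d / (2·SD)), with blinding index 2p − 1.

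The document gives no SD, so the values below are assumptions.

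| Assumed SD (min) | d = 4: p | Index | d = 9: p | Index |
|---|---|---|---|---|
| 3 | Φ(0.667) = 0.748 | 0.50 | Φ(1.5) = 0.933 | 0.87 |
| 5 | Φ(0.4) = 0.655 | 0.31 | Φ(0.9) = 0.816 | 0.63 |
| 10 | Φ(0.2) = 0.579 | 0.16 | Φ(0.45) = 0.674 | 0.35 |
| 15 | Φ(0.133) = 0.553 | 0.11 | Φ(0.3) = 0.618 | 0.24 |

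Chance is p = 0.50, index 0. For a given d and SD, these are the best an assessor could do from timing alone. Clearing time would raise d. An assessor who does not return, or who does not attend to the time, gains nothing.

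**The case against.** The strongest reply is that the sentence is a prohibition, not a permission. It sets a minimum condition and does not say that SOC assessors may or will come back early. Read with the Blinding section, under which assessors are to stay blinded, it can be applied as one rule for every case: leave before the reveal, return after clearance. A reader might infer that following the rule reveals the allocation with certainty, because an SOC assessor walks in on an open wound. The documents do not support that. It requires a return that the text nowhere describes and that the Blinding section argues against. This part of the objection stands. But even as a single rule, the time until theatre is clear still differs by arm, so a probabilistic cue remains.

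Return to theatre may also be rare. Complications are graded on in-patient days and at follow-up; Table 1 also marks adverse event assessment on the day of surgery, but nothing places it in theatre. This stands too: the frequency is unknown, and where nobody returns the rule does no harm.

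The guessing probabilities rest on an assumed SD and an ideal guesser, and synchronous procedures would add noise. That is right, and at 4 min with an SD of 10 to 15 min the result is close to chance.

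Two further replies carry less weight. This is a pilot without formal treatment comparisons, and the article admits that blinding may be hard to enforce. But that admission concerns the operating surgeon's post-operative review, and blinding is one of the things the pilot is there to test. The article also condenses a fuller protocol, and mentions a video and theatre sheets that may settle the detail. However, the return criterion is not left out of the article. It is stated, in a form that depends on the arm.

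**Conclusion.** The point holds in a limited form. The return criterion is written in terms of evidence that only the FS arm can produce, and the article offers none common to both arms, so the time of return can carry information about the allocation to assessors who should be blinded. The cue is mainly probabilistic. It rests on a timed difference of at least about 4 min before clearing, with 9 min reached only if the thaw does not overlap closure preparation at all. Its effect on guessing depends on the spread of closure times and on how often assessors return, neither of which is given. Certain disclosure would require an assessor to re-enter during an SOC closure; a literal reading of the rule does not prevent this, but the article does not say it will happen. The change is worth making because it protects a named pilot objective at almost no cost.

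**What to change.** Keep the clearance requirement and add conditions that apply equally in both arms. For example: *In both arms, clinicians who will assess outcomes stay out of theatre until the skin is closed, the same fixed minimum interval since the reveal has passed, and all signs of sealant use have been removed; otherwise they do not return for that case.*

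The interval should be long enough to cover the FS steps and clearing. If it is too short, closure and clearing in the FS arm will still decide when people return, and the cue will persist. The clearance condition should not be replaced by the interval alone, because an assessor could then enter while sealant equipment was still visible.

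The change needs one sentence in the protocol and a matching line on the theatre sheets, with no extra staff or procedures. The downside is that assessors stay out some minutes longer in SOC cases, which may be inconvenient when another procedure is performed in the same session.

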### Blinding

Patients, clinical outcome assessors, ward staff and research staff both centrally and at the site will be blinded to the allocation. Only members of the surgical team present in the theatre when the allocation is revealed will know which treatment arm the patient has been allocated to. These individuals are not permitted to inform colleagues or assess trial outcomes. The operation note, medical case notes and any other documentation that leaves the operating theatre will not state the allocation. The effectiveness of this blinding strategy will be assessed using blinding indices.

The patient will be unblinded if they suffer a serious adverse event and knowledge of the allocation is required for the ongoing medical management of the condition. It is unlikely that this trial will require unblinding as the FS is administered only once in the theatre environment. A severe hypersensitivity reaction, air embolism or transmission of an infective agent constitute a serious adverse event. If they occur, severe hypersensitivity and air embolism would be anticipated to occur during or immediately after administration in the theatre setting. Staff caring for the patient at this time will not be blinded, so there will not be a delay in diagnosis and emergency management.

In the event that the patient is diagnosed with an infectious disease that was not diagnosed pre-operatively, they will be unblinded. Based on the ‘Serious Hazards of Transfusion’ 2017 annual report [24], the following infectious diseases are known to have been transmitted via blood products in the UK:
Hepatitis A, B, C or EHuman immunodeficiency virus (HIV)Parvovirus (B19)Cytomegalovirus (CMV)Human T cell lymphotropic virus (HTLV) types I and IIMalariaVariant Creutzfeldt-Jakob Disease (vCJD) or any other prion disease

If the patient is newly diagnosed with any of the above infectious diseases, they will be unblinded and immediately referred to the appropriate medical specialists for treatment.

